### Statistical analyses

Forty participants is considered to be a suitable sample size for intervention pilot studies.^44^ This number of participants accounts for a likely small effect size between groups and an 80% powered definitive trial.^45^

For continuous outcome data from questionnaire data, data will be presented as mean (SD) or median (range). Comparisons will be made using a two-way repeated measures analysis of variance (ANOVA), with group as the between-participants factor and timepoint as the within-participants factor. This will be followed by post hoc t-tests if interaction is significant. Non-parametric data will be analysed using generalised estimation equation modelling. All tests will be two-sided and with alpha set at 0.05. Cohen’s *d* and *r* effect sizes will be calculated for parametric and non-parametric tests, respectively. We will also present a sample size calculation for a future definitive trial based on the primary outcome NQ results, and results regarding screening, recruitment and drop-out rates.

Additional exploratory analysis will be performed of between-group differences for the BPAT and Breathe-VQ due to the novelty of using these outcome measures in this population and because they may have important additional information on domains that are relevant to BPD.

No interim analyses are planned.

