**Methods and analysis:**

This is a study protocol for an assessor blinded 1:1 randomised controlled trial and qualitative interview study. Forty participants aged 18–40 years who score at least 19 on the Nijmegen Questionnaire (NQ) and do not have any underlying respiratory conditions will be recruited. Participants will be randomised to receive either physiotherapy-led or music therapy-led breathing exercises for 6 weeks. The primary outcome will be between-group difference in NQ post-intervention. Semistructured interviews with a purposive sample of participants will be performed. Qualitative data will be analysed using thematic analysis to better understand participants’ intervention and trial experiences.

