## Recruitment

### Online screening

Participants who register their interest to participate in the study will be sent an email asking them to complete the NQ,^10^ a patient-reported outcome measure that assesses functional respiratory complaints.^1 24^ The NQ has become the standard outcome measure used to identify BPD. Only participants who score at least 19 at screening^1 18^ will continue onto the study and repeat the questionnaire at their baseline assessment and post therapy.

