#### Primary outcome

Between-group differences in change of NQ score post intervention (mean, SD, CIs and effect size).

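### The primary NQ comparison is worded two ways, and the planned two-timepoint ANOVA uses baseline NQ inefficiently; one baseline-adjusted ANCOVA settles both at almost no cost

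*Protocol article*

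**What the plan says.** All references are to the protocol article.

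- **Abstract, Methods and analysis:** "The primary outcome will be between-group difference in NQ post-intervention".
- **Primary outcome:** "Between-group differences in change of NQ score post intervention (mean, SD, CIs and effect size").
- **Statistical analyses:** "Comparisons will be made using a two-way repeated measures analysis of variance (ANOVA), with group as the between-participants factor" and timepoint as the within-participants factor. Then: "This will be followed by post hoc t-tests if interaction is significant". Also: "All tests will be two-sided and with alpha set at 0.05".
- **Online screening:** entrants pass an NQ threshold of 19, then "will continue onto the study and repeat the questionnaire at their baseline assessment and post therapy". The analysis therefore has two NQ timepoints, baseline and follow-up.
- **Sample size:** 40 in total, allocated 1:1, so 20 per arm. Statistical analyses also says that the NQ results will feed the sample size of a definitive trial.

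The article does not say which SD Cohen's *d* will use.

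**The concern.** A post-score difference and a change-score difference are two estimators with different standard errors and different SDs under an effect size. A reader of the results could meet either one labelled as primary. If both are available once the data are in, the choice can follow the result, and it carries through to the definitive trial's sample size.

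The planned model does not settle this well. Its interaction subtracts the whole baseline score, whatever the correlation between baseline and follow-up. When that correlation is modest, subtraction adds noise and widens the interval. In a 40-person pilot, the interval is the main quantitative product.

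**Working it through.** **Plan's own figure.** The only stated number is 40. It rests on pilot-size recommendations ("Forty participants is considered to be a suitable sample size for intervention pilot studies"), with no NQ difference, SD or correlation given, so there is no formula to reproduce. Below, n = 20 per arm, retention is complete, and ρ (the correlation of baseline with follow-up NQ) is assumed. Units are SDs of NQ.

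**1. What the ANOVA tests.** With two timepoints, the group-by-time F equals the squared two-sample t on change scores. A numerical check gave 1.078 for both. The planned test therefore matches the Primary outcome section and not the abstract.

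**2. How far the two wordings can part.** Post difference minus change difference equals the baseline difference. Its standard error is √(2/20) = 0.32 SD. The article expects a small effect without giving a number; if that means 0.2 SD (assumed), the gap can exceed the effect and the two estimates can differ in sign.

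**3. Precision with equal SDs at both times.** Variance of the group difference, in units of 2σ²/n:
- post score: 1
- change score: 2(1 − ρ)
- ANCOVA: (1 − ρ²) × [1 + 1/(N − 4)], where the last factor is 37/36 = 1.028 at N = 40

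The ANCOVA/change ratio is therefore (1 + ρ)/2 × 1.028. Half-width is t × √(variance × 2/20), with t on 38 df (change) or 37 df (ANCOVA).

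| ρ | Variance ratio | Half-width, change | Half-width, ANCOVA | CI narrower by |
|---|---|---|---|---|
| 0.3 | 0.67 | 0.76 | 0.62 | 18% |
| 0.5 | 0.77 | 0.64 | 0.56 | 12% |
| 0.7 | 0.87 | 0.50 | 0.46 | 6% |

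The gain is about 1% at ρ = 0.9 and nil at 0.95. Below ρ = 0.5 the change analysis is less precise than ignoring baseline, because 2(1 − ρ) exceeds 1.

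**4. Effect of screening on NQ.** Selecting on a score of at least 19 narrows baseline spread more than follow-up spread in most of the cases tried, so equal SDs are doubtful. Assume a normal population with mean 15 and SD 9. Truncation at 19 leaves a fraction k = 0.278 of the screening-score variance. Let r be the screening-to-baseline correlation and c the screening-to-follow-up correlation. Among those selected, relative to the population variance:
- baseline variance: 1 − r²(1 − k)
- follow-up variance: 1 − c²(1 − k)
- covariance: ρ − rc(1 − k)

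Example with ρ = 0.5, r = 0.8, c = rρ = 0.4: the values are 0.538, 0.884 and 0.269. Change variance = 0.538 + 0.884 − 2 × 0.269 = 0.884. ANCOVA variance = 0.884 − 0.269²/0.538 = 0.750. The ratio is 0.848, or 0.87 after the 1.028 factor, so the CI is about 7% narrower. The correlation among those selected is 0.39; putting that into the equal-SD formula would give 0.70 and overstate the gain.

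Taking ρ from 0.3 to 0.7, r from 0.7 to 1.0, and c equal to either rρ or ρ, the ratio at N = 40 runs from 0.72 to 0.98, a CI 1% to 15% narrower. The gain is below the equal-SD figure in most of these cases, but not all: with ρ = r = c = 0.7 it is 11%, against 6%.

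**5. Carry-over to the definitive trial.** The SD of change is √[2(1 − ρ)] = 1.18, 1.00 and 0.77 at ρ = 0.3, 0.5 and 0.7. A true difference of 0.5 post-score SD therefore becomes d = 0.42, 0.50 or 0.65 on the change scale. With n per arm = 2 × variance × (1.960 + 0.842)²/0.5² = 62.8 × variance (large-sample, rounded up):

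| ρ | Post | Change | ANCOVA |
|---|---|---|---|
| 0.3 | 63 | 88 | 58 |
| 0.5 | 63 | 63 | 48 |
| 0.7 | 63 | 38 | 33 |

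**6. ANCOVA removes the choice of estimator.** With baseline as covariate, modelling follow-up or modelling change gives the same group coefficient, standard error and p-value (check: −1.867, 1.427 and 0.199 both ways).

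**The case against.** The abstract is a one-line summary. The full outcome definition and the planned interaction agree with each other, and under randomisation both wordings target the same expected difference. Correcting the abstract alone would remove the contradiction without changing the model. That stands, and it makes ANCOVA an improvement rather than a necessary correction.

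Four stronger readings are tempting, and the article does not support them:

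- **That the ANOVA throws baseline away or is biased.** It uses baseline with a fixed slope of 1 and is unbiased under randomisation. Simulated type I error at 20 per arm was about 5%.
- **That the estimate and CI appear only if the interaction is significant.** The Primary outcome section promises them without condition; the gate covers only the post hoc t-tests. What remains is that those t-tests are not specified and would seldom run: at 0.2 SD and ρ = 0.5, power is about 9%.
- **That the group main effect would be read as the treatment effect.** Doing so would halve the effect, but the article nowhere says it will be done.
- **That ANCOVA is worth 54%, 33% or 18% more participants.** Those figures come from 1/[(1 + ρ)/2] − 1 at ρ = 0.3, 0.5 and 0.7. They need equal SDs and ignore the cost of estimating the slope, and screening makes equal SDs doubtful.

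Finally, the stated progression threshold is 66% completion, which does not depend on the NQ test.

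**Conclusion.** The point holds as a recommended improvement. The primary outcome has two wordings that give different numbers in any one sample, and the article leaves open which SD defines Cohen's *d*. The planned test is valid but usually less precise than it could be. The likely gain is a confidence interval roughly 1% to 15% narrower given NQ screening, or 6% to 18% if baseline and follow-up SDs are equal.

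These sizes rest on an assumed ρ of 0.3 to 0.7, full retention, the assumed screening population, and the NQ threshold in Online screening applying to all entrants. Treatment could also change follow-up spread in either direction. Nothing here makes the planned test wrong or blocks the pilot.

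**What to change.** - Word the abstract and the Primary outcome section alike: follow-up NQ compared between arms by ANCOVA, adjusted for baseline NQ.
- Always report the adjusted mean difference with its 95% CI, whether or not any interaction is significant.
- State which SD is used for Cohen's *d*, and base the definitive-trial calculation on the same definition.
- Use the same model for BPAT and Breathe-VQ.
- Delete the post hoc t-tests that depend on a significant interaction.

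Cost: one paragraph of wording and one degree of freedom. No new data are needed, since baseline NQ is already collected.

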#### Secondary outcomes

##### Feasibility

Number of individuals completing both arms of the RCT study. At least 66% completion will support using that intervention in a future definitive randomised controlled study. The study team determined that below a 66% completion rate would either indicate significant changes to the study design are required prior to performing a definitive trial, or that a further definitive study is not feasible depending on other outcome analysis.Percentage of individuals recruited from screening, according to use of Nijmegen and BPAT screening tool.Perceived participant experiences of interventions and the feasibility of the study design, collected via semistructured interview.

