### Safety reporting

Adverse events will be recorded and followed up until resolved.

Individuals who return a positive lateral flow test and subsequent PCR test at any stage after consent to the study will be withdrawn from continuing in the study due to the known respiratory complications arising from COVID-19.^47^

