### Discontinuation

All participants are free to withdraw at any time from either intervention. Reasons for withdrawal will be collected and timing will be recorded because this information will help plan for the future definitive study. Withdrawn subjects will not be replaced on the trial.

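### With two timepoints, the fixed repeated-measures ANOVA is an unadjusted change-score comparison in participants with both NQ scores: open to bias if loss depends on baseline differently by arm, and less precise than a baseline-adjusted analysis

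*Protocol article*

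**What the plan says.** The primary outcome is "Between-group differences in change of NQ score post intervention". For continuous questionnaire data, Statistical analyses states: "Comparisons will be made using a two-way repeated measures analysis of variance (ANOVA", "with group as the between-participants factor and timepoint as the within-participants factor". A significant interaction is followed by t-tests. The alternative route is: "Non-parametric data will be analysed using generalised estimation equation modelling". No baseline covariate is named.

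Under Online screening, participants who pass screening "repeat the questionnaire at their baseline assessment and post therapy". The analysis therefore has two NQ timepoints.

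Three places bear on missing follow-up:

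- Safety reporting: participants with confirmed COVID-19 "will be withdrawn from continuing in the study".
- Discontinuation: "Withdrawn subjects will not be replaced on the trial".
- Feasibility: "At least 66% completion will support using that intervention" in a later definitive trial.

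The NQ results are also to be used to size that trial.

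**The concern.** A group-by-time ANOVA on two timepoints compares mean change between arms. Someone with a baseline but no follow-up NQ adds nothing to that comparison unless a value is imputed, and nothing in the model corrects for a baseline difference between the arms among those who remain.

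Participants know their allocation, and the two therapies differ visibly (predominantly phonated against unphonated exercises). The arms could therefore lose different kinds of people. If one arm loses its more severe participants and the other does not, those remaining in the first arm start lower and have less room to regress towards the mean. That arm then appears to improve less even when the therapies are equally effective. The article expects a small between-group effect, so a modest bias could be of similar size. The same completers' change and SD would feed the definitive trial's sample size.

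**Working it through.** **Inputs from the article.** 40 participants randomised 1:1 (20 per arm); baseline and follow-up NQ; group-by-time ANOVA; two-sided alpha 0.05. The sample size rests on cited pilot recommendations, with no difference, SD or dropout rate given, so there is no planned figure to reproduce.

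**Assumptions (not in the article).** Normal scores with equal SD at both times; baseline to follow-up correlation r of 0.4 to 0.7; loss of 10% to 34%; log-odds of loss changing by 1 per baseline SD; an SD of 6 points where results are in NQ points; no true difference.

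**Step 1: what the test is.** With two timepoints, the interaction F equals the squared t on change scores. A numerical check gave 0.0394 for both.

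**Step 2: where bias comes from.** Write follow-up = a + b × baseline + d × arm + error, and let D be the between-arm difference in mean baseline among completers. The expected change-score contrast is d + (b − 1) × D, so the bias is (b − 1) × D. It is zero if D = 0 (loss related to baseline equally in both arms) or if b = 1. Adjusting for baseline estimates d directly. With equal SDs, b = r.

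**Step 3: size.** Simulation with 1,000,000 subjects per scenario gave D in points; dividing by 6 gives SD units. In the one-arm pattern, loss in the other arm is at the same rate but random. Bias = (1 − r) × |D|.

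| Loss | Pattern | \|D\| points | \|D\| SD | r = 0.4 | r = 0.5 | r = 0.7 |
|---|---|---|---|---|---|---|
| 10% | one arm | 0.54 | 0.090 | 0.054 | 0.045 | 0.027 |
| 10% | opposite | 1.08 | 0.180 | 0.108 | 0.090 | 0.054 |
| 20% | one arm | 1.04 | 0.173 | 0.104 | 0.087 | 0.052 |
| 20% | opposite | 2.08 | 0.347 | 0.208 | 0.173 | 0.104 |
| 34% | one arm | 1.70 | 0.283 | 0.170 | 0.142 | 0.085 |
| 34% | opposite | 3.42 | 0.570 | 0.342 | 0.285 | 0.171 |

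The directly simulated contrasts agree: at 34% loss and r = 0.5 they were 0.85 and 1.71 points, that is 0.14 and 0.28 SD. Equal baseline-related loss gave a bias of zero within simulation error. ANCOVA on the same completers gave at most about 0.03 points in every scenario.

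**Step 4: type I error** (20 per arm, 34% loss, r = 0.5). Equal loss 4.9%; one arm 6.3%; opposite directions 10.8%.

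**Step 5: precision with no loss.** In units of the NQ variance, a change score has variance 2(1 − r) and a baseline-adjusted score 1 − r². At r = 0.5 these are 1.0 and 0.75. The ratio is (1 + r)/2, so 0.70, 0.75 and 0.85 at r = 0.4, 0.5 and 0.7.

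**Step 6: the 66% figure.** 1 − 0.66 = 34% is nominal. In whole participants, 0.66 × 20 = 13.2 means at least 14 of 20, or at most 6/20 = 30% lost. For the whole trial, 0.66 × 40 = 26.4 means at least 27 of 40, or at most 13/40 = 32.5% lost.

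**Step 7: loss that depends on the unseen outcome.** Suppose loss is 34% against 10%, leavers do not change and completers improve by 10 points (the article's threshold for clinically relevant change). The all-randomised mean improvements are 0.66 × 10 = 6.6 and 0.90 × 10 = 9.0, a difference of 2.4 points. The ANOVA shows about 0. A likelihood model with a common baseline mean shows about 0.05, so it misses the difference too.

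**The case against.** Several stronger readings are tempting, and the article does not support them.

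- *The plan accepts 34% loss.* A reader might infer this from the 66% figure, but that is a threshold for carrying an intervention forward, neither a forecast nor a tolerated amount of missing NQ. The Qualitative study section defines non-completers of the interventions by attendance and exercise adherence, and such a person can still return and complete the NQ. The 34% rows are therefore a nominal upper case.
- *Any loss related to baseline severity biases the result.* Not under a constant effect: the relation must differ by arm. The article does not predict that it will, and it describes dose and contact time as similar.
- *Dropping people without follow-up is the cause.* In these scenarios it is not. ANCOVA drops the same people and is unbiased, so the cause is the lack of baseline adjustment.
- *A missing-data rule is absent.* The article does not bar imputation, and such a rule may stand in a fuller document. Its absence is no finding. The point here concerns the method that is named.

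It is also fair to say that the bias is modest beside the pilot's uncertainty. At 34% loss about 13.2 remain per arm, and the standard error, √(2(1 − r) × 2/13.2), is 0.43 SD at r = 0.4 and 0.30 SD at r = 0.7. One-arm bias is then about 0.4 to 0.3 standard errors (0.170/0.43 and 0.085/0.30). Only the opposite-direction case is sizeable.

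The GEE route can keep baseline-only records. However, it applies only to non-parametric data, so a distribution check could change who is analysed, and standard GEE is not fully robust to missing-at-random loss.

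**Conclusion.** The point holds in a limited form. The named ANOVA is an unadjusted change-score contrast in participants with both scores. It is exposed to bias when loss depends on baseline differently by arm and the slope is below 1: about 0.03 to 0.11 SD at 10% loss and 0.09 to 0.34 SD at 34%. These ranges rest on the assumed correlations and loss mechanism. If the follow-up SD exceeds the baseline SD, the slope moves nearer to 1 and the bias shrinks.

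The loss of precision needs no dropout at all: the adjusted variance is 15% to 30% lower at r = 0.7 to 0.4. This is a worthwhile improvement to a pilot, not a flaw that invalidates it.

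Two limits apply to the remedy. If the treatment effect varies with baseline, even equal loss shifts the estimate (about 0.5 points in one simulated example), and ANCOVA without an interaction does not remove this. Non-ignorable loss, as in the 2.4-point example, is not handled by any of these main models.

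**What to change.** In Statistical analyses, replace the repeated-measures ANOVA for NQ, Breathe-VQ and BPAT with a baseline-adjusted analysis by allocated arm. Either of two forms will do:

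- a likelihood-based mixed model with time, group-by-time, a common pre-randomisation mean and unstructured covariance, which keeps every randomised participant, including those with a baseline score only; or
- ANCOVA of the follow-up score on arm and baseline score.

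Add one sensitivity analysis for NQ that shifts the unobserved follow-up values over a range set separately for each arm, including no change from baseline, and report where the conclusion changes. It is needed because the main model does not address non-ignorable loss.

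The change needs no new data or participants. Its downside is a missing-at-random assumption in the main model and slightly more analysis work.

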### Randomisation

Following the baseline screening/initial assessment, individuals will be randomised on a 1:1 basis based on a computer-generated random sequence generated using random.org, either to music therapist-led breathing exercises or physiotherapy-led breathing exercises (the next subsection details these interventions). Randomisation will be performed by an independent member of staff not involved in baseline or follow-up assessments and confirmation of group allocation will be provided online. The assessor will be blinded to which group the participants have been randomised to. Participants will be instructed to not disclose which intervention arm they have been allocated to. Should their intervention become known to the assessor at any time, another researcher will perform the follow-up assessment. Due to the nature of the interventions, it is impossible to blind participants to the intervention.

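### GEE is named for non-parametric data and paired with an r effect size, but it is a large-sample model of means, no rank test is named, and uncorrected it would run slightly above its 5% level at this sample size

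*Protocol article*

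**What the plan says.** All of this is in the Statistical analyses section of the protocol article. For continuous questionnaire outcomes the main method is given as: "Comparisons will be made using a two-way repeated measures analysis of variance (ANOVA), with group as the between-participants factor and timepoint as the within-participants factor". The next method named is: "Non-parametric data will be analysed using generalised estimation equation modelling". The error rate is fixed by: "All tests will be two-sided and with alpha set at 0.05". Cohen's d and r are then assigned in that order: "effect sizes will be calculated for parametric and non-parametric tests, respectively".

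The article does not say what makes data non-parametric. It names no rank test. It gives no link, working correlation, variance estimator or reference distribution for the GEE.

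**The concern.** Two things do not fit together.

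First, the label. Methods can be non-parametric; data cannot. GEE is not a rank, exact or distribution-free method. It models means and takes its inference from large-sample theory. An r effect size is ordinarily derived from the z statistic of a rank test. GEE produces regression coefficients, so the planned r has no source.

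Second, the benefit. If NQ scores look skewed and the analysis moves from ANOVA to an identity-link GEE, the estimated quantity is unchanged. Only the standard error and the reference distribution change. In a trial of 40 people, the common software form of that standard error is too small. The p-value and confidence interval of the primary outcome would then lean slightly towards finding a difference. The NQ results also feed the planned sample size calculation for the definitive trial.

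**Working it through.** **Inputs from the protocol article**
- 40 participants (Statistical analyses), and "individuals will be randomised on a 1:1 basis" (Randomisation): about 20 per arm.
- Completion threshold (Feasibility): "At least 66% completion will support using that intervention in a future definitive randomised controlled study". 0.66 × 40 = 26.4, about 26 participants or 13 per arm. This is used only as a low-end illustration.
- Two-sided alpha 0.05, so z = 1.96.
- Two NQ timepoints, baseline and post therapy (Online screening; Follow-up assessment).

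The figure of 40 rests on a cited pilot-size recommendation, with no difference or SD given. There is therefore no calculation to reproduce, and this point does not depend on one.

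**Assumptions, not in the protocol:** identity link, complete data, equal arms, uncorrected sandwich variance, z reference. The outcome distributions in step 4 are also assumed.

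**Step 1. Same contrast.** Let D be a participant's change in NQ. The GEE group-by-time coefficient is mean(D) in one arm minus mean(D) in the other. The ANOVA interaction F is the square of the two-sample t statistic on D, with 2n − 2 degrees of freedom.

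**Step 2. Size under normality.** Per arm, the uncorrected sandwich variance is Σ(D − mean)²/n². The t test uses Σ(D − mean)²/[n(n − 1)]. The ratio is (n − 1)/n, so the GEE test rejects when |T| > 1.96 × √((n − 1)/n), with T on 2n − 2 df.
- n = 20: 1.96 × √(19/20) = 1.910; P(|T₃₈| > 1.910) = 0.0637.
- n = 13: 1.96 × √(12/13) = 1.883; P(|T₂₄| > 1.883) = 0.0719.

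**Step 3. Interval width under normality.** The ratio of the GEE interval to the t interval is 1.96 × √((n − 1)/n) / t₀.₉₇₅,₂ₙ₋₂.
- n = 20: 0.944, about 6% too narrow.
- n = 13: 0.912, about 9% too narrow.

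**Step 4. Non-normal data.** Rejection rates under no difference, 100,000 simulated trials per row:

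| Assumed data | n per arm | Uncorrected, z | t-based (ANOVA interaction) | Mancl-DeRouen, z | Mancl-DeRouen, t |
|---|---|---|---|---|---|
| Normal | 20 | 0.064 | 0.050 | 0.052 | 0.045 |
| Normal | 13 | 0.071 | 0.049 | 0.052 | 0.042 |
| Lognormal | 20 | 0.055 | 0.040 | 0.042 | 0.035 |
| Lognormal | 13 | 0.061 | 0.039 | 0.041 | 0.031 |
| NQ-like, truncated at 19 | 20 | 0.063 | 0.050 | 0.051 | 0.044 |
| NQ-like, truncated at 19 | 13 | 0.071 | 0.050 | 0.052 | 0.042 |
| BPAT-like counts | 20 | 0.063 | 0.049 | 0.051 | 0.044 |
| BPAT-like counts | 13 | 0.072 | 0.049 | 0.052 | 0.041 |

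A separate recomputation gave 0.061 and 0.069 for exponential data and 0.051 and 0.057 for lognormal data (20 and 13 per arm). The t-based test there was between 0.035 and 0.050. Over all scenarios the uncorrected test lies between 0.051 and 0.064 at 20 per arm, and between 0.057 and 0.072 at 13.

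In this setting the Kauermann-Carroll correction multiplies the variance by n/(n − 1). With a t reference it coincides with the t-based column.

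**Step 5. Fitted GEE.** Exchangeable GEE fits to lognormal data, 1,500 runs per setting, gave 0.059 in each of three settings: 20 per arm complete, 20 per arm with 34% missing follow-up, and 13 per arm. The bias-reduced variance gave 0.044, 0.038 and 0.043. The Monte Carlo standard error is √(0.059 × 0.941/1500) = 0.006, so these runs agree with step 4 but could not establish the excess alone.

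**The case against.** The strongest reply is that the error rates rest on choices the protocol never makes. Variance estimator, small-sample correction and link are commonly left to an analysis plan, which is not shown, and their absence is not a fault here. That stands, so the error rates are conditional.

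GEE also has merits. It does not assume normality, it allows other links, and it can use baseline data from participants without follow-up, which a complete-case ANOVA does not. The GEE sentence is not tied expressly to the primary outcome either. It may be meant for ordinal or binary outcomes, such as the two responder percentages among the secondary outcomes. All of this stands, and it is why GEE need not be removed.

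A reader might infer four stronger things that the document does not support:
- That the fallback is simply less valid than the ANOVA. This is shown only for type I error of the uncorrected z test on the mean-change contrast.
- That the primary p-value will be wrong by the normal-theory amounts whenever the fallback is used. Those figures are for normal data. Strongly skewed data gave smaller excesses, down to 0.051 at 20 per arm.
- That the switch is an unplanned second route to the p-value. It is stated in advance, although its trigger is not defined in the article.
- That 13 per arm is the expected analysed number. It is only the feasibility threshold.

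Finally, this is a pilot, and the stated threshold for taking an intervention forward is a completion rate. That limits the consequence. It does not repair the mismatch between GEE, the non-parametric label and r, which is in the stated text.

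**Conclusion.** The point holds in a limited form. Without any assumption, the section labels a mean-based, large-sample method as the one for non-parametric data, and it promises an r for tests it does not name. For the two-timepoint NQ change with an identity link and complete data, moving to GEE leaves the estimated difference unchanged, so the fallback gains little.

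If the uncorrected sandwich and a z reference were used, the excess over the nominal 5% would be about 0.1 to 2.2 percentage points across the distributions tried, while the t-based test stays at or below 5% within simulation error. This is a modest inflation that a standard correction removes. It rests on equal arms and on assumed outcome distributions, since the protocol gives no SD or shape for the NQ.

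**What to change.** 1. Pre-state one primary analysis of NQ that does not depend on how the data look, for example follow-up NQ adjusted for baseline NQ. Add a permutation p-value, drawn according to the allocation scheme actually used, as the named robustness check.
2. If GEE is kept for any outcome, say which outcome and link. Specify a small-sample corrected variance, such as Kauermann-Carroll or Mancl-DeRouen, with a t reference.
3. Drop r, or name the rank test it belongs to. Replace the reference to non-parametric data with the outcomes meant.

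The cost is a few sentences of analysis wording and a permutation run of seconds. The small downside is that Mancl-DeRouen with a t reference is slightly conservative: 0.042 to 0.045 for normal data and 0.031 to 0.035 for lognormal data in the table above.
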